#### Outcome adjudication

Incidence of MACE occurring within 30 days of ED attendance will be recorded on a serious adverse event (SAE) form by the local principal investigator or designee with reference to relevant clinical information and responses to 30-day follow-up telephone assessments uploaded to the study database. All participant data will be reviewed by an independent adjudication committee at the end of the study to confirm the primary outcome.

### Sample size

Current observational research gives estimates of the proportion of patients with an hs-troponin <LoD in the intervention group of the RCT (LoDED strategy) of between 10% and 60%.^11–17^ UK observational data suggest that these patients will be discharged within a median time of 3.5 hours (taking into account laboratory processing and 60 min of decision-making time).^10^ Data provided to us from a recent pragmatic RCT evaluating a 0/2-hour hs-troponin rule-out strategy have demonstrated that only 10% of patients will be discharged within 4 hours using this approach.^9^ Clinical protocols using rule-out strategies at later time points (eg, 3 hours) will be expected to have even fewer patients discharged within the 4-hour time frame; similarly the 0/1-hour strategy may realise a marginal increase in discharges before 4 hours. These differences have been taken into account within the power calculation. For the overall population we anticipate 8% will be discharged within 4 hours using usual care and at least 17% using the LoDED strategy. Therefore, this study will be powered to detect a 9% difference between the early discharge rates with 90% power and 5% statistical significance. This will require 282 patients in each group and 564 patients in total with primary outcome data. Assuming a 95% follow-up rate, 594 patients need to be recruited. Recruitment will take place over a 9-month period.

### Data analysis

All analyses will be conducted blind to group allocation. A Consolidated Standards of Reporting Trials diagram will be used to report the number of patients screened, recruited and randomised.^27^ It will also detail the number allocated to each group and the frequency of the primary outcome.

The primary outcome of discharge within 4 hours will be analysed by logistic regression using all those randomised in an intention-to-diagnose analysis. The analysis will be stratified by centre to allow for differences between the proportions discharged within 4 hours in the control group at each of the study sites. Heterogeneity of the odds of early discharge at each centre will be investigated and only pooled if appropriate. The OR of early discharge controlling for age, sex and centre will be presented with a 95% CI for each centre individually and combined across centres. In the event of significant heterogeneity in the control group but homogeneity within the intervention group the results will be presented as the rate of early discharge in the intervention group together with 95% CIs. Adherence to the allocated rule-out strategy will be presented as percentage with 95% CIs.

The analysis of the quantitative secondary outcomes will also control for age, sex and centre, with a multiple regression analysis and difference in means reported for the comparison of length of hospital stay between groups and for the total score from the patient satisfaction survey obtained from summing the individual items. The responses for the individual items of the patient satisfaction survey will also be reported by group, but an adjusted analysis will not be carried out.

The incidence of MACE occurring within 30 days of ED attendance in those discharged according to the LoDED strategy versus usual care will also be reported with 95% CIs. As the event rate is expected to be low, it is unlikely to be possible to carry out an adjusted analysis. There are no preplanned interim analyses. A secondary per-protocol analysis will also be performed for the primary outcome.

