## Methods and analysis

### Study design and conduct

This is a pragmatic, multicentre, randomised controlled parallel group trial in adult patients presenting to the ED with suspected cardiac chest pain and who trigger the chest pain investigation pathway. Five hundred and ninety-four participants will be randomised in a 1:1 ratio to be managed according to the LoDED strategy (allowing discharge after a single hs-troponin test at presentation to ED if a participant has no new ischaemic ECG changes and the hs-troponin is below the LoD) or the usual care rule-out strategy in current clinical use at each study site. Usual care will usually include two hs-troponin blood tests taken between 1 and 6 hours after presentation and may vary between sites.

This is an open study. Participants’ study allocations will only be blinded to those performing central review of data for the assessment of outcomes and the statistician analysing the results. All patients will be consented and randomised before their initial hs-troponin results are known. Patients will be ineligible to participate in the trial once the initial hs-troponin result is known to the treating clinician in order to prevent selection bias. The decision to discharge a patient will be made after clinical assessment by the treating clinician. In the event of ongoing clinical concern, the clinician may proceed with further testing and/or admission at their discretion, and contrary to the allocated strategy. Information on protocol adherence will be collected to facilitate a per-protocol analysis as well as the primary intention-to-treat analysis.

The key objective of this study is to conduct a randomised controlled trial (RCT) of the LoDED strategy versus usual care to compare the proportion of patients successfully discharged within 4 hours of arrival, with no MACE during the following 30 days. We will also measure admission rates, hospital bed usage, length of stay, resource use and patient satisfaction, facilitating a health economic evaluation, and determine whether the LoDED strategy is acceptable to patients through qualitative interviews.

Day-to-day trial management is administered through the UKCRC-registered Peninsula Clinical Trials Unit (CTU) at Plymouth University and sponsored by North Bristol NHS Trust.

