#### Baseline blood sampling

All participants will have a blood sample taken for hs-troponin measurement on, or shortly after, ED arrival as part of the standard clinical assessment of patients with chest pain. No additional blood sampling is required for study purposes. All study centres have access to hs-troponin assays which already form part of standard care.

Given the pragmatic nature of the trial, ‘presentation’ blood sampling will be defined as the first blood sample taken after arrival in the ED. Blood sample results will not be delayed for trial purposes.

Standard laboratory reporting of hs-troponin results and other routine baseline blood tests will be used for both clinical assessment and for data collection purposes. At all sites this is through an electronic clinical record. Data from the laboratory system will be anonymously recorded within the case report form (CRF).

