#### LoDED strategy (intervention)

Participants randomised to the LoDED strategy will be eligible for discharge after a normal ECG and single hs-troponin test at presentation to the ED if the hs-troponin is below the LoD for the assay in use at the study centre.

Any participant not fulfilling this discharge criterion will revert to the existing rule-out strategy in use at that study site and have a second hs-troponin test after 1–6 hours as per usual care.

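### The primary model adjusts only for the randomisation factors and omits initial hs-troponin below the LoD, a missed efficiency that leaves the planned 90% power intact

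*Protocol article*

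**What the plan says.** The Data analysis section specifies logistic regression on all randomised participants, stratified by centre. On the reported effect it says: "The OR of early discharge controlling for age, sex and centre will be presented with a 95% CI". These covariates are the factors used in allocation (Randomisation section: stratified by centre, minimised on age and gender). No troponin term is named.

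Other sections make the initial troponin result available for everyone and independent of allocation:

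- Baseline blood sampling: "All participants will have a blood sample taken for hs-troponin measurement on, or shortly after, ED arrival". The same section has laboratory data entered in the case report form.
- Study design and conduct: "All patients will be consented and randomised before their initial hs-troponin results are known".
- LoDED strategy (intervention): early discharge needs a normal ECG and a first result below the assay's LoD. Otherwise, "Any participant not fulfilling this discharge criterion will revert to the existing rule-out strategy in use at that study site".

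Below-LoD status is also used elsewhere. It determines the 30-day follow-up route, who completes the EQ-5D and the health-economic subgroup.

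**The concern.** The LoDED strategy can alter management only for participants below the LoD. Ischaemic ECGs are excluded at entry, so LoD status is nearly the whole discharge criterion. The Introduction puts the share eligible for early discharge at 25% to 34%, depending on the assay. If the planned 9-point effect arises in about 30% of participants, early discharge in the LoDED arm must be far more common below the LoD than above it.

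That makes LoD status probably the strongest available predictor of the primary outcome in that arm. A model without it treats this variation as noise and does not correct a chance difference between arms in the below-LoD share, on which randomisation neither stratifies nor minimises. At stake is some power and some precision of an absolute effect, obtainable from data the trial already holds.

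**Working it through.** **1. Reproduce the plan's figure.** The inputs are in the Sample size section: early discharge of 8% in the control group against 17% or more with LoDED, a target difference of 9 points, 90% power and a 5% significance level. Its result is: "This will require 282 patients in each group and 564 patients in total with primary outcome data". Recruitment is then set at 594 to allow for 5% loss to follow-up. With two-sided 5% significance (sidedness assumed), pooled variance under the null and no continuity correction:

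n = [1.960·√(2·0.125·0.875) + 1.2816·√(0.08·0.92 + 0.17·0.83)]² / 0.09² = (0.9167 + 0.5938)² / 0.0081 = 281.7, so 282 per group.

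564 / 0.95 = 593.7, so 594. Power at 282 per group is 90.0%. The stated size is right and relies on no covariate.

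**2. Rates by LoD status.** The protocol does not give these. Assumptions: share below the LoD q = 0.30; overall control rate 8%; control rate below the LoD k times the rate above it; the whole 9-point effect falls below the LoD. Then the control rate above the LoD is 0.08 / (0.3k + 0.7), and the LoDED rate below the LoD is the control rate there plus 0.09 / 0.30 = 0.30.

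| k | Control below / above | LoDED below / above |
|---|---|---|
| 1 | 8.0% / 8.0% | 38.0% / 8.0% |
| 2 | 12.3% / 6.2% | 42.3% / 6.2% |
| 5 | 18.2% / 3.6% | 48.2% / 3.6% |

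**3. Variance of the standardised risk difference.** Let d₀ and d₁ be the below-minus-above differences in the control and LoDED arms. The unadjusted variance is (0.0736 + 0.1411) / 282 = 0.2147 / 282. Standardising over LoD status removes approximately q(1−q)(d₀ + d₁)² / (2·282), so the proportional reduction is 0.21·(d₀ + d₁)² / (2·0.2147):

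- k = 1: 0.21·0.300² / 0.4294 = 4.4%
- k = 2: 0.21·0.423² / 0.4294 = 8.8%
- k = 5: 0.21·0.591² / 0.4294 = 17.1%

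Simulation (10,000 trials per scenario, 282 per arm) gives 4%, 8% and 16%.

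**4. Power.** The same simulations, likelihood-ratio test, arm alone against arm plus below-LoD indicator:

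| k | Arm only | Arm + LoD status |
|---|---|---|
| 1 | 90.5% | 91.3% |
| 2 | 90.7% | 92.7% |
| 5 | 91.0% | 95.0% |

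The gain is 0.8 to 4.0 points within the simulation, or 1.3 to 5.0 points against the nominal 90%.

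**5. The planned OR.** From 6,000 simulated trials per scenario at q = 0.30:

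| k | OR, arm only | OR, adjusted | SE of log OR, arm only | SE of log OR, adjusted |
|---|---|---|---|---|
| 1 | 2.38 | 2.48 | 0.274 | 0.281 |
| 2 | 2.40 | 2.62 | 0.275 | 0.288 |
| 5 | 2.38 | 2.86 | 0.274 | 0.302 |

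The SE rises. Power improves because the conditional OR moves further from 1 than the SE grows: the mean z goes from 3.13 to 3.20, 3.16 to 3.31 and 3.14 to 3.45. The same expected z needs 564·(z unadjusted / z adjusted)², or about 540, 515 and 466 evaluable patients.

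**6. Chance imbalance.** The SD of the between-arm difference in the below-LoD share is √(2·0.3·0.7 / 282) = 3.9 points. A 5-point imbalance split evenly between arms moves the risk difference by 0.025·(d₀ + d₁). This is 0.75 points with a flat control rate and 0.025·(0.386 + 0.086) = 1.2 points with rates of 44% / 5.4% and 14% / 5.4%. At k = 5 it is 0.025·0.591 = 1.5 points. The SE of the difference is √(0.2147 / 282) = 2.8 points.

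**The case against.** The strongest reply is that nothing in the section is wrong. Adjusting for the randomisation factors is standard, the trial has its planned power without more, and a statistical analysis plan that is not shown could add covariates. This stands as far as it goes: the point is an available improvement to a covariate set that the protocol states, not a fault in it.

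A reader might infer that the planned OR has a wider interval than the data allow. The documents and the calculation do not support that. The OR is the only effect measure named for the arm comparison, and the SE of its logarithm rises on adjustment. The precision gain belongs to a marginal measure.

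A reader might also infer that imbalance in the below-LoD share biases the result. It does not: chance imbalance is covered by the unadjusted interval, and the likely shift is well under one SE.

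Three further objections stand in part:

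- The simulations leave out age, sex and centre. If these already predict LoD status, the gain over the stated model is smaller.
- One common adjusted OR fits poorly if the effect lies below the LoD. With 44% against 14% the OR there is about 4.8, and it is 1 above. This is why results by LoD status should accompany it.
- About 282·0.08 + 282·0.17 = 70 events are expected in all, so a further covariate could strain the per-centre models. The change should be confined to the combined analysis.

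That the result is read after randomisation is no objection. It comes from the routine first sample, and allocation cannot change its value.

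**Conclusion.** The point holds as a missed efficiency. The stated model omits a baseline value that is recorded for everyone, is unaffected by allocation and is the intervention's own trigger. With 30% below the LoD and an assumed control association of 1 to 5 times, adjustment is worth roughly 1 to 5 points of power and a 4% to 17% lower variance for a standardised risk difference. Both ranges rest on rates by LoD status that the protocol does not give, and on the effect arising wholly below the LoD.

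It would be wrong to conclude that the trial is underpowered, that the sample size needs changing or that the analysis as written is invalid. The gain is modest; what justifies acting is that it costs almost nothing.

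**What to change.** Amend the Data analysis section, or the analysis plan, before unblinding:

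- For the combined all-centre primary analysis, fit the logistic model to all randomised participants with age, sex, centre and initial hs-troponin below the LoD of the site's assay (yes/no).
- Report the risk difference standardised over these covariates, with its 95% CI, alongside the OR.
- Show the arm comparison separately below and above the LoD.
- Leave the per-centre ORs as planned.
- Keep the age, sex and centre model as a sensitivity analysis.

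The cost is a few sentences, with no new data, patients or visits. The one downside is that the conditional OR will differ numerically from the one now planned. The report should explain this, with the standardised difference and the sensitivity analysis beside it.

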#### Usual rule-out strategies (control)

Usual care varies between study sites but includes ECG on arrival and usually two hs-troponin tests. All sites take the first sample at presentation, but the minimum time delay between the two samples varies. The existing rule-out strategy in use at each study site will be documented at study commencement and filed in the relevant investigator site file.

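### A heterogeneity rule in the Data analysis section would, on its natural reading, replace the randomised comparison with a single-arm discharge rate, and it conflicts with the sentence before it

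*Protocol article*

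**What the plan says.** The key objective (Study design and conduct) is to compare the two arms on successful discharge within 4 hours. The Sample size section powers that comparison: "we anticipate 8% will be discharged within 4 hours using usual care and at least 17% using the LoDED strategy", that is, a "9% difference between the early discharge rates with 90% power and 5% statistical significance".

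The Data analysis section specifies logistic regression stratified by centre, and gives the reason: control-group discharge proportions may differ between sites. It continues: "Heterogeneity of the odds of early discharge at each centre will be investigated and only pooled if appropriate". It then promises, without condition, an odds ratio adjusted for age, sex and centre with a 95% CI, for each centre and combined. The next sentence covers the case of significant heterogeneity in the control group with homogeneity in the intervention group. In that case "the results will be presented as the rate of early discharge in the intervention group together with 95% CIs".

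Elsewhere the protocol makes clear that usual care differs by site. The section on usual rule-out strategies says: "All sites take the first sample at presentation, but the minimum time delay between the two samples varies". The Sample size section puts early discharge at 10% under 0/2-hour testing, lower with later second samples and marginally higher with 0/1-hour testing. The Discussion says sites were selected for their differing usual-care pathways.

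**The concern.** The rule lets a heterogeneity test decide what is reported as the main result, and one branch leads to a rate with no comparator. Three things make this a badly set rule.

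- **The trigger is a feature the design expects.** Sites were chosen for variable pathways, and the protocol itself predicts different control rates under them.
- **The remedy does not fit the problem.** Differing control rates are differing baselines, and a centre-stratified analysis allows for them. The check relevant to a differing treatment effect is treatment-by-centre interaction. A significant test in one arm and a non-significant test in the other is not that check.
- **The outcome of the rule cannot serve the trial.** An intervention-group rate does not show whether LoDED beats usual care. Nor can it show the additional 9% of early discharges on which the Conclusions would base widespread uptake.

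**Working it through.** **1. The plan's own figure.** Inputs from the Sample size section: 8% v 17%, 5% significance (taken as two-sided), 90% power, 1:1 allocation. With pooled variance and mean rate 0.125:

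n = [1.96·√(2·0.125·0.875) + 1.2816·√(0.08·0.92 + 0.17·0.83)]² / 0.09² = [1.96·0.4677 + 1.2816·0.4634]² / 0.0081 = 281.7, so 282 per group.

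564 / 0.95 = 593.7, so 594. Both stated figures are reproduced: "This will require 282 patients in each group and 564 patients in total with primary outcome data". The sample size is not at issue.

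**2. What the reader would see at the design rates.**

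- Comparison kept: risk difference 0.09 ± 1.96·√(0.08·0.92/282 + 0.17·0.83/282), giving 9 points (95% CI 3.6 to 14.4). Crude odds ratio (0.17/0.83)/(0.08/0.92) = 2.36.
- Rule fired: 0.17 ± 1.96·√(0.17·0.83/282), giving 17% (95% CI 12.6% to 21.4%), with nothing to set it against.

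**3. How often the rule would fire.** The document gives neither the number of centres, nor their control rates, nor the heterogeneity test. Assumed here: 4, 6, 8 or 10 equal centres; 282 per arm (70, 47, 35 or 28 per arm per centre after rounding down); control rates evenly spaced with mean 8%; intervention rate 17% everywhere. The rule fires when a chi-square test across centres gives p < 0.05 in the control arm and p ≥ 0.05 in the intervention arm. At least 20,000 trials were simulated per scenario.

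| Control rates across centres | 4 centres | 6 | 8 | 10 |
|---|---|---|---|---|
| 8% everywhere | 4.6% | 4.4% | 4.1% | 4.4% |
| 5% to 11% | 17% | 12% | 10% | 9% |
| 4% to 12% | 28% | 18% | 14% | 13% |

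The first row is close to the nominal 0.05 × 0.95 = 4.75%: with no heterogeneity anywhere, the rule can still fire by chance.

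**4. Whether the comparison needed rescuing.** A centre-stratified Cochran-Mantel-Haenszel test at two-sided 5% has power of 0.90 to 0.91 in all these scenarios. Among the simulated trials in which the rule fires, its power is still 0.87 to 0.92. The chance that a significant comparison is obtained and also presented is overall power minus the part lost to the rule. With control rates of 4–12%, that is about 0.905 − 0.28·0.89 = 0.66 with 4 centres and 0.905 − 0.13·0.89 = 0.79 with 10.

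**5. Type I error.** When the rule fires no between-arm test is presented, so it can only remove rejections: P(reject and not fired) ≤ P(reject). In simulations with no treatment effect, rejection with the rule applied was 3.4% to 5.0%.

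**The case against.** **The text does not say that only the intervention rate is reported.** This is correct. The preceding sentence promises the combined odds ratio without condition, and the CONSORT diagram will give the frequency of the primary outcome. The claim that the comparison is certain to be withheld therefore goes beyond the text. But no sentence says the odds ratio stays the main result once the rule fires, and saying that the results will be presented as a single-arm rate naturally reads as a replacement. On the milder reading, the two sentences still have to be reconciled.

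**The trigger has two conditions.** Intervention-group homogeneity is also required. This offers little protection, because a truly homogeneous arm passes a 5% test about 95% of the time.

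**Varying control rates with a constant intervention rate do imply varying effects.** That is true, and it is the best reason for such a rule. The answer is to describe effects by centre beside the overall contrast, not to drop the comparator.

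**The article is condensed.** The test and its threshold may be defined in the SAP. Their absence is not the complaint; the rule itself is stated affirmatively.

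Two stronger readings fail. A reader might infer that choosing the estimand after a test invalidates the 5% level; step 5 shows that it does not. A reader might also infer a contradiction with "All analyses will be conducted blind to group allocation". Within-arm tests can be run on masked labels, and only the choice of which coded rate to present needs the key, so the blinding point is minor.

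**Conclusion.** The concern holds in this form: the Data analysis section contains a rule that, read naturally, substitutes a single-arm rate for the randomised comparison, and that at the least conflicts with the sentence before it. The single-arm rate cannot answer the stated objective, and the 90% power does not carry over to it.

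Under the stated assumptions the rule fires in about 4% of trials with no control heterogeneity, 9–17% with control rates of 5–11%, and 13–28% with 4–12%. These spreads are in keeping with the Sample size section. Wider ones make firing more frequent, but a centre rate such as 16% is hard to square with a marginal increase over 10%, so the verdict does not rest on them. All firing rates depend on the assumed number and size of centres and on the assumed test. The conclusion that the rule discards a comparison that still works does not depend on the exact rate: stratified power stays near 90% throughout. The loss is the comparison itself, not control of type I error.

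**What to change.** Delete the single-arm fallback. State that the comparison of all randomised participants, adjusted for centre, age and sex and with a 95% CI, is the primary result whatever any heterogeneity test shows. This also settles how the sentence on pooling is to be read. A risk difference alongside the odds ratio would match the scale on which the trial was powered. Report the treatment-by-centre interaction and the arm-specific rates by centre as descriptive supplements.

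The cost is a wording change in the protocol or SAP before unblinding. It needs no extra patients, data or visits, and the sample size stands.

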There are two hs-troponin assays currently approved by the National Institute for Health and Care Excellence (NICE): Roche hs-troponin T and Abbott hs-troponin I.^7^ The majority of centres within the Limit of Detection of Troponin and ECG Discharge (LoDED) study use the Roche hs-troponin T assay, reflecting current UK practice (information from manufacturer). The LoD for this assay is <5 ng/L. Some centres use the Abbott hs-troponin I assay with LoD of <2 ng/L. In addition, an emerging hs-troponin I assay (Beckman Coulter Access hs-troponin I) meets criteria to be defined as a high-sensitivity assay but is yet to be evaluated by NICE.^20^ Similarly, the LoD for this assay is <2 ng/L. Performance of all three assays at the LoD appears similar, with similar proportions of patients being eligible for safe early discharge.^15–17 21^ The LoD alone does not have the required diagnostic accuracy for clinical implementation.^13^ However, combining the LoD with ECG findings improves diagnostic accuracy (the LoDED strategy). In a meta-analysis of over 9000 patients evaluating the LoDED strategy with hs-troponin T, pooled sensitivity for 30-day major adverse cardiac events (MACE) was 98.0% (95% CI 94.7% to 99.3%), with 30% of patients eligible for early discharge.^16^ For the Abbott hs-troponin I assay, an analysis of 3155 patients showed a pooled sensitivity for MACE of 97.9% (95% CI 95.4% to 99.2%), with 25% of patients eligible for discharge.^15^ For the Beckman hs-troponin I assay, sensitivity for the rule-out of AMI has been shown to be >99%, in an analysis of 1871 patients, with 34% of patients eligible for discharge.^17^ These data demonstrate the efficacy (safety) of the LoDED strategy, yet they are all from observational cohort studies, where no patient was discharged based on their recommendations; therefore, the clinical effectiveness of the LoDED strategy across populations remains unknown.

The 2016 update to the NICE ‘chest pain of recent onset’ guidelines also supports the use of hs-troponin with a cut-off at the LoD. However, the strategy recommended by NICE requires that the LoD cut-off be combined with a risk score,^22^ such as the Thrombolysis in Myocardial Infarction (TIMI) score,^23^ rather than a normal ECG as we propose in the LoDED strategy. External validation of the NICE approach demonstrated that approximately 15% of patients will be suitable for early discharge, in contrast to approximately 30% using the LoDED strategy.^21^

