### Outcomes

#### Primary outcome

The primary outcome is successful early discharge, defined as discharge from hospital within 4 hours of ED arrival, without MACE occurring within 30 days.

The safety endpoint of MACE occurring within 30 days, included within the primary outcome, will be defined as cardiac death, AMI or emergency revascularisation occurring within 30 days of ED attendance (including the index presentation). AMI will be defined according to the universal definition, which states that a rise and/or fall of troponin above the 99th percentile value confirms the diagnosis.^25^ A significant rise and/or fall will be defined as an absolute change in troponin over time of at least half the 99th percentile value of the assay in clinical use.^26^

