#### Secondary outcomes

Secondary outcomes will include: length of ED/EDOU stay, measured in hours, hospital admission and subsequent length of stay, incidence of MACE occurring within 30 days of ED attendance, comparative costs, participant satisfaction (quantitative survey) and acceptability to patients (qualitative methodology).

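### The planned 30-day MACE comparison is not randomised: its LoDED side is the group discharged under the rule, and its comparator is unclear

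*Protocol article*

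**What the plan says.** Secondary outcomes lists "incidence of MACE occurring within 30 days of ED attendance" with no restriction to any subgroup. Data analysis states how it will be handled: "The incidence of MACE occurring within 30 days of ED attendance in those discharged according to the LoDED strategy versus usual care" is to be reported with 95% CIs. It adds that an adjusted analysis is unlikely to be feasible because few events are expected.

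The discharge rule is in the section on the LoDED strategy: "Participants randomised to the LoDED strategy will be eligible for discharge after a normal ECG and single hs-troponin test at presentation to the ED", provided that the troponin is below the LoD. It continues: "Any participant not fulfilling this discharge criterion will revert to the existing rule-out strategy in use at that study site". Study design and conduct says that randomisation comes before the first troponin result is known. That section and Clinical management leave the discharge decision to the treating clinician. The Primary outcome section counts MACE from the index presentation onwards.

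**The concern.** Randomisation protects a comparison of arms, or of subgroups defined identically in both arms by something that allocation cannot affect. The LoDED side here is neither. To enter it, a participant must have a very low troponin, a qualifying ECG and a clinician willing to discharge. LoDED-arm participants who fail the rule drop out of that side, and their events go with them. Because index events count as MACE, a rule-out test is designed to keep most events out of the discharged group.

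The trial hopes for wide adoption of the strategy, and this is the only standalone MACE comparison that the article states. A reader could take it as randomised evidence on safety, which it would not be.

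**Working it through.** **The plan's own figure.** The article gives no figure for the MACE comparison. Its sample size for the primary outcome reproduces and supplies the arm size used below. For 8% versus 17%, mean 12.5%, two-sided 5% and 90% power: n = [1.960 × √(2 × 0.125 × 0.875) + 1.282 × √(0.08 × 0.92 + 0.17 × 0.83)]² / 0.09² = 281.7, so 282 per group and 564 in total. Then 564/0.95 = 593.7, so 594, or 297 per arm.

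**Is the LoDED side the arm or a subset?** Participant advice uses the same wording for the people who are sent home under the rule and receive the leaflet. When the article means the arm, it speaks of being managed under the strategy (Study design and conduct; Trial interventions). Data analysis specifies everyone randomised for the primary outcome, and Health economic analysis does so for costs. Nothing equivalent is stated for MACE. The LoDED side is therefore a subset.

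**Reading A: LoDED discharges versus the whole control arm.** Suppose the strategy has no effect on MACE, and treat those eligible under the rule as those discharged. With overall MACE risk p, the risk among the eligible is (1 − sensitivity) × p / eligible share. Dividing by p removes it:

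- Risk ratio under no effect = (1 − sensitivity) / eligible share.
- hs-troponin T (Introduction: pooled sensitivity "was 98.0% (95% CI 94.7% to 99.3%), with 30% of patients eligible for early discharge"): 0.020/0.30 = 0.067. Over the sensitivity interval: 0.007/0.30 = 0.023 to 0.053/0.30 = 0.177.
- Abbott hs-troponin I (Introduction: 97.9%, 25% eligible): 0.021/0.25 = 0.084.

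The article gives no MACE rate for this trial, so absolute risks are assumptions. The Introduction's statement that 90% of chest pain is benign is not a MACE rate. Values from 3% to 15% were tried with the hs-troponin T figures. Each null trial was simulated 4,000 times, with 297 controls and about 89 LoDED-eligible participants (30% of 297):

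| Assumed control MACE | Eligible subset | Apparent difference (points) | Fisher's test significant at 5% |
|---|---|---|---|
| 3% | 0.20% | −2.8 | 10% |
| 5% | 0.33% | −4.7 | 55% |
| 10% | 0.67% | −9.3 | 95% |
| 15% | 1.0% | −14.0 | nearly 100% |

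The subset's observed rate was below control in at least 99% of runs at every assumed rate.

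**Reading B: LoDED discharges versus usual-care discharges.** Both sides are now selected after randomisation, by different rules: one presentation result below the LoD, or whatever the local serial pathway requires. The LoDED side has a stricter troponin limit, and the usual-care side has usually passed a second test. The article gives no MACE rate among usual-care discharges, so neither the size nor the direction of the bias can be worked out.

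**Does the primary composite fill the gap?** Only in part. MACE after discharge within 4 hours turns a success into a failure and is counted by allocation. A participant discharged later, or admitted, has already failed the composite, so MACE in that participant changes nothing.

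**Precision.** With zero events the exact upper 95% limit is 1 − 0.025^(1/n): 4.1% for n = 89, 7.1% for n = 50 (17% of 297) and 1.2% for n = 297.

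**The case against.** A reader might infer that the plan is bound to make LoDED look safer, or even to show real harm as benefit. The article does not support this, because it follows only under Reading A. Reading B is at least as natural, and under it harm from single-test discharge could show as higher MACE on the LoDED side. The remark about a low event rate fits Reading B somewhat better: at 10%, a control arm of 297 would have about 30 events. It does not settle the matter, since at 3% there would be about 9.

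The risk ratio is also borrowed. It combines the LoD with the ECG in observational cohorts, whereas Box 1 excludes ischaemic ECGs before randomisation, so part of that discrimination may already be used up. The Introduction itself says that the LoD alone is not accurate enough. The range 0.02 to 0.18 reflects the cohort sensitivity interval and is not a range for this trial.

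It would be too strong to call this the trial's only between-group safety comparison, because the composite captures MACE after early discharge by allocation. Nor is any MACE test or ratio planned, and an unseen SAP may add an analysis by arm. These points limit the size of the claim. They do not make the stated population a randomised one, and that population is written down rather than left open.

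**Conclusion.** The concern stands in a limited form. The standalone MACE comparison that the article states is not randomised on either reading, its comparator is ambiguous, and its population does not match the unrestricted outcome under Secondary outcomes. Under Reading A, selection alone would favour LoDED, with an illustrative null risk ratio of about 0.07. This assumes that the cohort sensitivity and eligible share apply and that eligible participants are the ones discharged. With ischaemic ECGs already excluded the true figure may differ, though it should still lie well below 1. Under Reading B no figure can be given. The powered primary analysis is unaffected.

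**What to change.** - State that 30-day MACE will be compared by allocated arm in all randomised participants, with a CI for each arm and for the risk difference (exact or score method).
- As a supporting analysis, compare participants with a presentation hs-troponin below the LoD in both arms, by allocation. Every participant has that sample as standard care, and below-LoD participants in both arms get the same 30-day contact. Note the limitation that AMI requires a rise and/or fall in troponin, while LoDED discharges may have only one result. AMI ascertainment can therefore differ between arms, and this also affects the whole-arm comparison.
- Report MACE among LoDED discharges as a single-group miss rate, without a usual-care comparator.
- Reconcile the wording of Data analysis and Secondary outcomes.

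The cost is a change of wording, with no new data. The safety figure becomes less favourable and rests on few events. As a rough guide, with 297 per arm and equal rates, the 95% half-width for the risk difference is 1.96 × √(2 × p × (1 − p)/297): about 2.7 points at an assumed 3%, 3.5 at 5% and 4.8 at 10%.
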